### Data assessment

Data will be collected at the ED, in participants’ homes, in the geriatric university outpatient clinic and at the gait laboratory. Furthermore, Inertial Measurement Units (IMUs) to measure physical activity as well as gait parameters will be worn by the participants during daily life over seven days at each time point (T1 – T3). After the initial assessment, the researchers maintain contact with the participants through monthly phone calls, as part of the prospective falls recording in addition to fall calendars (Fig. 1). First data assessment will be within four weeks of presenting to the ED. Whereas participants in Arm 1 will be visited at home for the first functional assessment (T1), participants in Arms 2 and 3 will be assessed in the geriatric university outpatient clinic and additionally via telephone interview. Data collection after the intervention (T2) and twelve months after presenting to the ED (T3) will be scheduled at participants’ homes.

### Outcome measures

As part of a comprehensive geriatric assessment, participants’ characteristics, i.e. demographic data, socioeconomic status, medical history, medication use, sensory and mobility aid use, and lifestyle factors will be recorded. A detailed fall history, including circumstances and consequences of the most recent falls, will be collected. Validated instruments will be used to evaluate fall risk, functional status, cognitive performance, depressive symptoms, physical activity, and health-related quality of life. Exercise participation and adherence will be monitored and falls will be tracked throughout the follow-up period. Additionally, sensor-based data regarding physical activity will be collected. An overview of all assessment tools and time points is provided in Table 2.

**Table 2 Tab2:** Assessment battery during the emergency department Visit, home visits, geriatric university outpatient Clinic, visits and training sessions

Assessment tool	Outcomes	Timepoint
1. Risk stratification	Age, gender, country of birth, highest level of education, level of care, living situation, medical care, capacity to get up after falling	Emergency department
2. Specific fall history	Time of fall, location of fall, activity before falling, direction of fall, injuries, loss of consciousness, capacity to get up after fall	T1/ clinic^+^
3. Socioeconomic status	Income, education [34], occupation [34], satisfaction with living situation [35]	T1/ clinic^+^
4. Participants’ characteristics (including personal and medical history)	Usage of hearing, seeing and walking aids, living situation, smoking status, alcohol consumption, medication, joint replacements.	T1/ clinic^+^, T2, T3
5. Fall risk assessment tool (FRAT-up) [36]	Total risk score (ranging from 0–1)	T1, T2, T3
6. (instrumental) activities of daily living a. Lawton’s and Brody’s Index [37] b. Barthel Index [38] c. Jonkmann Index [39]	Total score (ranging from 0–8) Total score (ranging from 0–100) Total score (ranging from 0–18)	T1/ clinic^+^, T2, T3
7. Functional performance: a. Hand grip strength test [40] b. Single leg stance test [41] ** c. Short Physical Performance Battery Test (SPPB) [42]**	Grip strength measured in kg Duration in seconds Total score (ranging from 0–12)	T1/ clinic^+^, T2, T3
8. German short falls efficacy scale (short FES-I) [43, 44]	Total score (ranging from 7–28)	T1/ clinic^+^, T2, T3
9. Montreal Cognitive Assessment (MoCA) [45] a. MoCA memory index score (MoCA-MIS) [45, 46]	Total score (ranging from 0–30) Total score (ranging from 0–15)	T1/ clinic^+^,T2, T3
10. Trail Making Test A and B (TMT A + B) [47]	Duration until completion in seconds & number of mistakes	T1/ clinic^+^,T2, T3
11. Longitudinal Urban Cohort Ageing Study (LUCAS - FI) Functional Ability Index (LUCAS - FI) [48]	Functional ability classified in: Robust, postRobust, preFrail, Frail	T1/telephone interview^++^, T2, T3
12. Physical activity: a. German-Physical-Activity-Questionnaire 50+ (PAQ-50+) [49] b. Physical Activity Scale for the Elderly (PASE) [50] c. Activity monitor (activPAL^©^) worn for 7 days	Energy expenditure per week Total score (ranging from 0–793) Number of steps, total active / inactive time	T1, T2, T3
13. German Life Space Questionnaire (LSA-D) [51, 52]	Total score (ranging from 0–120)	T1/telephone interview^++^, T2, T3
14. Depressive Symptoms a. Depression in Old Age Scale (DIA-S) [53] b. Cornell Depression Scale [54]*	Total score (ranging from 0–10) Total score (ranging from 0–38)	T1/ clinic^+^, T2, T3
15. Health-related quality of life EQ-5D – 3 L + EQ-5D Visual Analogue Scale [55, 56]	Total score (ranging from 0–15)	T1/ clinic^+^, T2, T3
16. Loss of Balance documentation	Total number of balance losses during daily life, self-reported for seven days	T1, T2, T3
17. Fall Calendar	Total number of falls during the follow up period	Monthly phone calls
18. Training characteristics a. Borg scale [57]	Frequency of participation in training, duration and contents of training Total score (ranging from 6–20)	Every training session
19. Perturbation training characteristics*** a. Perceived difficulty and anxiety [33]	Gait speed, duration of training session, type of perturbations, number of perturbations, dynamic reactive balance Total score (ranging from 1–5)	Every gait lab training session

* The Cornell Depression Scale will be used instead of the DIA-S in case of severe cognitive impairment (MoCA < 18) or an existing diagnosis of dementia

** During the functional assessments, participants will be equipped with three wirelessly synchronized IMUs(Opal V1, Mobility Lab™, APDM, Inc., Portland, OR, USA), which will objectively assess postural sway and gait characteristics [58, 59]

*** During the gait lab visits, participants will wear the IMUs, alongside an activPAL monitor (activPAL4™, PAL Technologies Ltd., Glasgow, UK), as well as a wrist-worn IMU (Axivity AX6, Axivity Ltd., Newcastle upon Tyne, UK) and a smartphone (Galaxy A52, Samsung Electronics Co., Suwon, South Korea) positioned on the body

Clinic^+^: arm 2 and 3, baseline parameters are assessed at the geriatric university outpatient clinic

Telephone interview^++^, parameters are collected via telephone interview

### Focus groups

To explore preferences, needs, facilitators, and barriers associated with the implementation of secondary falls prevention in clinical settings, as well as to evaluate participants’ acceptance of the implementation process from a patient-centered perspective, focus group interviews will be conducted as part of the study [60]. The study aims to recruit 72 individuals, including participants, relatives/caregivers and stakeholders, who will be assigned to twelve focus groups (six with participants, three with relatives, three with stakeholders), which is in line with previous approaches [22].

Informed consent for potential participation in a focus group will be obtained during the initial home visit or at the university outpatient clinic. The consent form will ask participants to specify whether they agree to be contacted again for this purpose. Participants who consented to be contacted for participation in a focus group will then be chosen purposefully, depending on criteria like their study arm, to create matching group constellations to engage discussions.

During the initial home visit or visit in the geriatric university outpatient clinic, participants will be offered a flyer inviting relatives to participate in a focus group discussion. Relatives may voluntarily reach out and, upon agreeing to take part, will receive an informed consent form to confirm their participation. Similarly, members of relevant organizations will also receive flyers inviting them to participate in focus groups. If they make contact, the necessary informed consent documentation is provided.

Focus groups will last 90 min and participants of the focus group will receive financial compensation for the spent time. Audio data from the focus group interviews will be transcribed with two multidisciplinary independent researchers analyzing the data. Content analysis according to Kuckartz [61] will be applied with categories such as needs, preferences, barriers, and facilitators deductively derived from the Theoretical Domains Framework [62] and the Consolidated Framework for Implementation Research [63]. Furthermore, categories will be derived inductively from the material recorded [64].

### Sensor data acquisition and machine learning

In the historical control study SeFallED, machine learning algorithms were developed to automatically detect gait disturbances induced by standardized perturbations in the gait laboratory [65]. Subsequent work demonstrated that everyday wearable devices positioned at typical body locations, such as smartphones and hearing aids, can also support automatic detection of such disturbances [66, 67]. In the iSeFallED study, those algorithms, in particular deep convolutional long short-term memory network (DeepConvLSTM), will be further refined using an extended perturbation protocol that incorporates varying perturbation intensities and a larger number of repetitions (Table 1); these modifications are expected to enhance algorithm robustness and generalizability. Furthermore, different approaches will be explored: spectrogram-based analyses will be applied to identify characteristic temporal-frequency signatures, and anomaly-detection methods will be explored to prescreen events of interest.

The following sensor systems will be worn during the treadmill perturbation-based balance training sessions performed in the laboratory. Treadmill-based sensor instrumentation will include: a thigh-worn accelerometer (activPAL4, PAL Technologies Ltd., Glasgow, UK); an inertial measurement unit (IMU) comprising accelerometer, gyroscope and magnetometer (Opal V1, Mobility Lab, APDM Inc., Portland, OR, USA) worn at six body positions (feet, wrists, lumbar and sternum); a wrist-worn device resembling a smartwatch position with accelerometer and gyroscope (Axivity AX6, Axivity Ltd., Newcastle upon Tyne, UK); a hearable device with integrated accelerometer (Cosinuss c-med° alpha, Cosinuss GmbH, Munich, Germany); and a smartphone (Galaxy A52, Samsung Electronics Co., Suwon, South Korea) to capture accelerometer data similar to a phone worn in the right pocket of the trouser. The Opal IMU and the hearable device will be used exclusively in the laboratory and will not be deployed in at-home monitoring.

The at-home component of the study is exploratory and specifically aims to assess whether perturbations detected in the laboratory can also be transferred in everyday life using everyday wearable devices and following up on previous work by Feld and colleagues [66, 67]. For this purpose, a convenience sample of approximately 100 participants - consistent with prior work by Hellmers and colleagues [65] - will be monitored continuously for seven consecutive days. In the at-home monitoring phase, participants will wear the wrist-worn activity monitor (Axivity AX6, Axivity Ltd., Newcastle upon Tyne, UK), a thigh-worn activity monitor (activPAL4, PAL Technologies Ltd., Glasgow, UK), and carry a smartphone (Galaxy A52, Samsung Electronics Co., Suwon, South Korea). These IMUs and the smartphone will continuously record movement data over the full seven-day period. To aid in identifying episodes of balance loss, participants will keep a daily diary documenting any occurrences of loss of balance (for example, tripping, slipping, or stumbling). The combined laboratory and at-home datasets will enable (1) within-laboratory algorithm refinement across multiple body positions and sensor types, and (2) an exploratory assessment of the detectability of gait perturbations in real-world settings.

### Safety

All serious adverse events (SAEs) and adverse events (AEs) will be documented using study-specific adverse event reporting forms. Overexertion during training will be mitigated by offering modifications for strenuous exercises and implementing Borg’s RPE scale, which has been shown to be feasible for older adults with and without cognitive impairment [29, 68]. The individualized nature of the training protocol will accommodate the heterogeneous needs of participants, ensuring a tailored approach.

In particular, treadmill perturbation-based balance training will be guided by a scale that considers both perceived difficulty as well as anxiety levels, as previously recommended for applying treadmill perturbation-based balance training [33]. Additionally, participants will be regularly asked whether they feel fit to continue, and they may request a break at any time if needed. If subjective or objective indicators of overexertion are observed, the training session will be paused. All adverse events will be promptly reported to the principal investigator.

### Statistical analysis and sample size calculations

Descriptive analyses will summarize participant characteristics, including age, sex, place of residence, level of education, and intervention choice. Differences between groups in these characteristics, as well as adherence to the assigned or selected interventions and the proportion of participants who attend the health sport activities, will be explored to assess feasibility and representativeness.

Feasibility of the training interventions will be assessed by documenting AEs and SAEs, as well as dropout rates, while acceptability will be evaluated through focus groups. The effectiveness of the tailored interventions in the iSeFallED study will be analyzed using a Wilcoxon-Mann-Whitney test, comparing endpoints between the historical control group (SeFallED) and the new study population. The primary outcome will be the change in Activities of Daily Living (ADL) scores between T2 (6 months) and T3 (12 months) using ADL scores from Jonkman and colleagues [39].

An independent statistician performed the sample size calculation to assess effectiveness. This calculation was based on data from 257 participants in the previous SeFallED project, who were followed over a 12-month period. For the iSeFallED study, it was assumed that the tailored interventions would result in a clinically meaningful improvement of at least 1 point in ADL score in individuals with at least a moderate risk of functional decline [39]. No difference is expected for individuals in Arm 1 (mild risk) compared to the historical control group. Data from the previous study indicated that approximately one-third of participants exhibited a low risk of functional decline (Arm 1), while two-thirds had at least a moderate risk (Arms 2 and 3). Consequently, an expected difference (Δ) of 0.67 points in the ADL score was determined for the new study (iSeFallED).

To detect a meaningful difference in ADL scores between T2 and T3 with a power of 90% at a significance level of α = 0.05, a total of 246 participants is required. Accounting for an estimated dropout rate of approximately 20% (based on a 17% dropout rate in the previous study), the necessary sample size increases to 308 participants. To further strengthen the study’s robustness and allow for secondary, exploratory analyses, a total sample size of 350 participants is planned.

Secondary endpoints include fall rate, time to first fall, and the number of falls in relation to physical activity compared to the historical control group. This analysis aims to evaluate the effectiveness of the interventions in preventing further falls. Furthermore, socioeconomic factors will be analyzed at both the regional and individual levels. The effects of the secondary falls prevention program on further secondary endpoints such as health-related quality of life, life-space mobility, physical activity, and cognitive function will also be explored in comparison with the historical control group.

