## Methods

### Study design

The iSeFallED study is a pragmatic implementation trial utilizing a mixed-methods approach to evaluate the feasibility, acceptability, and effectiveness of a secondary falls prevention intervention for older individuals following a fall with presentation to the ED without subsequent hospitalization. Previous studies have reported participation rates of approximately 50% in falls prevention programs at 12 months [21]. To enhance adherence, participants in the current study are allowed to choose their preferred intervention. Consequently, a randomized controlled trial (RCT) design was deemed infeasible. Instead, a quasi-experimental design will be used, comparing outcomes with a historical control group from the prior observational SeFallED study, conducted between 2021 and 2025 [22].

Participants in the iSeFallED study will be followed for 12 months. The study will be conducted at the Carl von Ossietzky University in Oldenburg, Germany from October 2024 until September 2027, in accordance with the Declaration of Helsinki and was approved by the Medical Ethics Committee of the University of Oldenburg (number 2024–192). All participants will be asked to provide written informed consent to participate in the study. The consent forms are designed to be signed by either the participant or if needed by the participant and his / her legal representative. Ethical guidelines for research conducted with adults that lack the capacity to give consent will be followed and include the principle of group, the subsidiarity principle and the minimal risk standard [23]. Further, study information has been adapted to facilitate the participant’s understanding of the study, which will be provided in addition to the regular consent form, if necessary. Figure 1 shows the study design in a flow diagram.

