The iSeFallED study will employ the study participant cohort from the prior SeFallED study as a historical control group [82], thereby addressing the well-recognized recruitment challenges associated with vulnerable patient populations. This design allows the study to better reflect real-world clinical practice, as RCTs frequently exclude a substantial proportion of patients, and, thus, limit generalizability. By maintaining inclusion and exclusion criteria consistent with those used in the previous study, iSeFallED seeks to extend understanding of the clinical effectiveness of secondary falls prevention within routine healthcare contexts [27, 83]. While this approach increases the effective sample size and enhances external validity, several limitations must be acknowledged. Participants enrolled during the earlier study may have been subject to different global or local circumstances, which could influence outcome trajectories. To mitigate potential biases inherent to the use of historical controls [82, 84], the baseline characteristics between the two study populations will be systematically compared, and statistical models will be adjusted for any identified differences by the study biostatistician.

The findings of iSeFallED will inform the feasibility, acceptability, and effectiveness of a secondary prevention program for older individuals presenting to the ED after a fall but not requiring hospitalization. The study will also evaluate implementation success within the complex and resource-limited ED environment, offering opportunities to refine processes to improve outreach and inclusivity in healthcare services for older adults. Furthermore, it will refine automated gait disturbance detection using machine learning algorithms and assess its feasibility in real-life data. Through its mixed-methods design, iSeFallED has the potential to serve as a model for integrating secondary falls prevention interventions into clinical practice, ensuring accessibility and scalability for a broader population.

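### The only named effectiveness test takes no covariates, the Discussion promises data-dependent adjustment, and the plan does not say which gives the primary result

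*Protocol article*

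**What the plan says.** Protocol article, Study design: randomisation was judged infeasible, so "a quasi-experimental design will be used, comparing outcomes with a historical control group from the prior observational SeFallED study". The historical data were collected between 2021 and 2025.

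Statistical analysis and sample size calculations: effectiveness "will be analyzed using a Wilcoxon-Mann-Whitney test, comparing endpoints between the historical control group (SeFallED) and the new study population". The primary outcome is the change in the 0–18 ADL score from T2 (6 months) to T3 (12 months). Differences between groups in participant characteristics appear in this section only as something that "will be explored to assess feasibility and representativeness". They are not linked to the primary comparison.

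Discussion: the authors accept that participants in the earlier study "may have been subject to different global or local circumstances, which could influence outcome trajectories". They will compare baseline characteristics of the two cohorts, and "statistical models will be adjusted for any identified differences by the study biostatistician". Neither this section nor the statistical section names a model.

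**The concern.** The two sections describe different analyses of the same comparison. One takes no covariates. The other is adjusted, but only for what turns out to differ. A reader cannot tell which will be reported as the primary result.

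This matters because nothing in the design balances the cohorts. They come from different periods, and entry differs too. Under Recruitment process and Data assessment, Arm 1 has a home visit following the SeFallED protocol. Arms 2 and 3, expected to be two-thirds of participants, are referred to an outpatient clinic, where they can consent on site or by post. Their baseline is taken in the clinic and by telephone. People who take up that route may differ in prognosis from those who entered SeFallED.

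The adjustment rule has its own weakness. It selects covariates by observed imbalance, not by prognostic importance. A factor that matters for ADL trajectory but is not flagged as different would be left out, and the model and covariate set stay open after the baseline data are seen.

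**Working it through.** **1. The plan's own figures.** The statistical section says that "an expected difference (Δ) of 0.67 points in the ADL score was determined". This reproduces as 2/3 × 1 + 1/3 × 0 = 0.67. It also says that "with a power of 90% at a significance level of α = 0.05, a total of 246 participants is required". The dropout step reproduces: 246 / (1 − 0.20) = 307.5, rounded up to 308. The 246 itself cannot be checked, because no standard deviation (SD) is given and the text does not say whether 246 is the new cohort alone or both groups together.

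**2. Implied SD.** Taking the test as two-sided (sidedness is not stated), SD = 0.67 / [(1.960 + 1.282) × √(1/n₁ + 1/n₂)].
- 246 as both groups, 123 against 123: 0.67 / (3.242 × 0.1275) = 1.62.
- 246 new against 257 historical: 0.67 / (3.242 × 0.0892) = 2.32.

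With the Wilcoxon efficiency factor 3/π the values are 1.58 and 2.26, so the choice of formula matters little.

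**3. What a bias would do to the named test.** Assume 350 × 0.80 = 280 analysed in iSeFallED and 257 in SeFallED, with no true effect and a spurious difference b in the T2–T3 change. By normal approximation:

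SE = SD × √(1/280 + 1/257) = SD × 0.0864, which is 0.140 for SD 1.62 and 0.200 for SD 2.32.

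False-positive rate = Φ(b/SE − 1.96) + Φ(−b/SE − 1.96).

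| b (points) | SD 2.32 | SD 1.62 |
|---|---|---|
| 0 | 5% | 5% |
| 0.1 | 8% | 11% |
| 0.2 | 17% | 30% |
| 0.3 | 32% | 57% |

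For b = 0.2 and SD 1.62: b/SE = 1.43, so Φ(−0.53) + Φ(−3.39) = 0.298. With 246 against 257 the range at b = 0.2 is 16–28%. The values of b are chosen for illustration and have no source in the document.

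**4. Simulation of the test itself.** This used 246 against 257, no true effect, one normal covariate and 4,000 runs per setting. The columns give the share of runs that reject at 5%.

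| Covariate–outcome correlation | Imbalance (SD) | Wilcoxon | ANCOVA fixed in advance | Adjust only if imbalance is significant |
|---|---|---|---|---|
| 0.2 | 0.1 | 5.3% | 4.9% | 4.7% |
| 0.3 | 0.2 | 10.3% | 5.6% | 5.8% |
| 0.5 | 0.2 | 19.2% | 5.3% | 6.1% |
| 0.5 | 0.3 | 37.6% | 4.3% | 4.7% |

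The third row corresponds to a bias of 0.5 × 0.2 = 0.10 SD, or 0.16 to 0.23 points at the implied SDs. Its 19.2% is in line with step 3. Small or weakly prognostic imbalances do little harm.

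**The case against.** The Discussion recognises the bias of historical controls, commits to a baseline comparison and gives the adjustment to the biostatistician. The article condenses a fuller protocol, and an analysis plan may exist. A missing covariate list or model form would therefore be no finding, and that stands. But the named test and the imbalance-based rule are stated choices. An analysis plan that made either one primary would leave the other section wrong or unexplained. One can read the text as a headline test with adjusted models in support, but it does not say so, and on that reading the primary result is the unadjusted one.

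Eligibility is described as similar to SeFallED, recruitment builds on the earlier strategy, and a change score removes stable level differences. This also stands. It narrows the risk to differences in trajectory, calendar period and entry route, and does not remove it.

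A reader might infer three stronger things that the document does not support:
- **That the result is certain to be confounded, or that the 5% error rate fails.** The document supports only that the cohorts may differ. Size and direction are unknown, and a bias could equally hide a benefit.
- **That data-driven adjustment itself inflates type I error.** In the one-covariate simulation it did not (about 4–6%). Baseline data can also be compared before any T2 or T3 result exists. What remains is analyst freedom and omitted covariates.
- **That adjustment would roughly halve the variance.** The factor 1 − r² applies against the raw follow-up score. Against a change score with equal variances, adjusting for its starting value gives (1 + r)/2. At an assumed r = 0.7 that is 0.85, a 15% reduction. Here the starting value is T2, which should not be a covariate.

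A rank test is a reasonable choice for a bounded score, and it does not prevent a difference in points from being reported alongside it. The point concerns adjustment, not ranks.

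**Conclusion.** The point holds as an inconsistency with a real consequence. The protocol never uses the word unadjusted. That follows from the test it names and from the absence of any other effectiveness analysis in the Methods. The adjustment in the Discussion cannot be carried out with that test, depends on observed differences, and has no stated rank against it.

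The size is conditional. If the T2–T3 change differed spuriously by 0.2 points, about 30% of the planned 0.67 (0.2 / 0.67), the false-positive rate would be about 17–30% instead of 5%. This rests on an SD of 1.62 to 2.32, a two-sided test, 280 against 257 analysed, a normal approximation, and a bias that is assumed and not estimated. No corrected sample size can be computed, because neither the SD nor any covariate–outcome correlation is given.

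The primary effectiveness claim depends entirely on this comparison, so the text should be settled before outcome data are analysed.

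**What to change.** In the statistical section, name one covariate-adjusted primary analysis of the stated ADL change: a linear or ordinal regression on study (iSeFallED against SeFallED).
- Fix the covariates in advance on prognostic grounds and include them whether or not they differ: T1 ADL score, age, sex, and those risk variables listed under Recruitment process that were measured comparably in both cohorts. Use the individual variables and not the algorithm's classification, which was developed on SeFallED data.
- Do not adjust for T2 or later values, which are post-intervention.
- Report the adjusted difference with a 95% confidence interval. Keep the Wilcoxon-Mann-Whitney test as supportive and add propensity weighting as a sensitivity analysis.
- In the Discussion, replace the conditional adjustment sentence with a reference to the prespecified list.

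The cost is mainly wording, since the Implementation process section says that SeFallED underwent similar measurements. Two small burdens remain: checking that each covariate exists in comparable form in SeFallED, and accepting modelling assumptions for a bounded 0–18 score. Running both the linear and the ordinal form, one as primary and one as sensitivity analysis, would test the latter. Moving away from the T2–T3 endpoint, for example to T3 adjusted for T1, would be a separate decision and would need its own sample size.
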